### Study medication and dose

2.4

Metformin hydrochloride is a generic, FDA and EMA approved drug for treatment of patients with diabetes mellitus type 2. Its adverse events, interactions, risks and precautions are well-known. Metformin Hydrochloride 850 mg will be purchased as product with marketing authorization (MA) and repackaged. Matching placebo tablets will be produced under GMP conditions and distributed by a licensed company (Ardena). Taking into account doses used in preclinical studies, the maximum daily dose of 3000 mg, considerations of tolerance and available tablet dosing, the suggested daily dose for this trial is 850 mg administered thrice daily. Common adverse effects include diarrhea, nausea and abdominal pain. These can be largely mitigated by using a titration scheme and adhering to intake during or after a meal. In case the participant does not tolerate 3 tablets per day, the dose may be decreased to the maximum tolerable dose. Compliance and adherence to the study medication will be monitored through a diary. Following the conclusion of the clinical trial, the attending neurologist could consider the off-label prescription of metformin depending on the outcomes of the study.

### Outcome measures

2.5

#### Primary outcome measure

2.5.1

The primary outcome is the change in T25FW from baseline to 96 weeks of treatment.

#### Secondary outcome measures

2.5.2

Clinically relevant outcome measures will be assessed as secondary outcomes: Expanded Disability Status Score (EDSS) for general disability, Symbol Digit Modalities Test (SDMT) as a measure for information processing speed and 9-hole Peg test (9HPT) as a measure of hand function.

Furthermore, imaging outcome measures include brain MRI volumetrics (change in whole brain volume and gray matter volume, change in T2 lesion volume, change in T1 lesion volume) along with MRI DTI. Both volumetric MRI and DTI metrics are used as surrogate outcomes for disability in clinical trials (64, 65) and correlate well with disability progression in clinical practice (66, 67). For the DTI analysis, the following parametric maps will be extracted: fractional anisotropy (FA), mean diffusivity (MD) and radial diffusivity (RD). Measurements will encompass both white matter and lesion areas, with a voxel-wise longitudinal evaluation being conducted.

#### Tertiary outcome measures

2.5.3

Cost-effectiveness analysis of the metformin treatment will be conducted based on survey data on health-related quality of life, caregiver strain and healthcare resource usages. We adopt the societal perspective and make use of existing tools, such as a burden-of-illness questionnaire (69), the EQ-5D-5L, the Multiple Sclerosis Impact Scale (MSIS-29) and the Caregiver Strain Index (CSI).

As patients may not progress in all domains, a recently described composite outcome, the Overall Disability Response Score (ODRS) (70) will be evaluated as an additional exploratory outcome. Another clinical exploratory outcome will be the 2-minute walking test, as not all patients may be able to undertake this endurance assessment over time.

Susceptibility-weighted imaging will be analyzed in both the treatment and placebo arm. This allows the follow up of the presence, volume, number and destructiveness of “iron rim lesions” (IRLs), also known as “paramagnetic rim lesions”. Inflammatory lesions are seen as hyperintense lesions on T2 weighted images, while chronic lesions, also called ‘smoldering, paramagnetic or iron-rim lesions’ can be seen on T2* images as a hypo-intense rim, representing iron-loaded microglia or macrophages (25, 71–73). Together with DTI, this MRI technique offers valuable insights into the impact of metformin on MS disease mechanisms that may not be fully captured by solely assessing brain volume.

#### Substudies

2.5.4

Study patients will be asked to participate in optional substudies. Separate informed consent forms will be used to obtain written informed consent of the patient.

##### Adherence monitoring

2.5.4.1

This substudy is designed to monitor adherence to the study drugs through an online app (Remecare®). In case patients are unable to use an electronic device or are unwilling to use the online app, a paper diary will be provided to track study medication intake and adherence.

##### Centralized biorepository for biomarkers

2.5.4.2

In addition to clinical, conventional and non-conventional imaging outcome measures, biomarkers and biobanking of samples for later analysis are crucial components of a clinical trial in PMS, to improve the understanding of underlying disease and therapeutic mechanisms. In this substudy we will analyze neurofilament light chain and glial fibrillary acidic protein on the SIMOA platform within the study population. Besides, a biorepository will be set up for future- and re-use of the collected biological samples, including serum, plasma and DNA. This supplementary blood sample collection is scheduled to coincide with the routine blood sampling intervals conducted for safety monitoring and routine care.

## Analysis

3

A summary of baseline data with comparison of demographics (age, sex, ethnicity), clinical tests at baseline, concomitant therapies and disease duration between the metformin and placebo arm will be presented. For the health economic analysis, marital status, household composition/living situation and educational level will be recorded. In addition, a CONSORT flow diagram (74) will be produced to summarize the number of patients at each stage (eligibility, randomization, allocation, discontinuation and follow-up). Adverse events (AE), Serious adverse events (SAE) and Suspected Unexpected Serious Adverse Reaction (SUSAR) will be summarized per arm using descriptive statistics.

Analysis will be conducted based on the intention-to-treat population. If the data exhibit a normal distribution, the primary analysis will entail in first instance (to align with sample size calculation) an independent samples t-test to compare the alteration in T25FW from baseline to the end of the 96-week treatment period between the metformin and placebo arm. A secondary sensitivity analysis will include a linear regression model with 96-week T25FW as outcome and baseline T25FW as predictor, plus a linear mixed model with T25FW at all-time points as outcome (both models can take other confounders into account) to get a more precise estimate of the treatment effect. Similar linear regression and linear mixed models will be used to analyze the secondary and clinical tertiary outcomes at 96 weeks and over time. The cost effectiveness analysis will use the societal perspectives, including both direct and indirect, medical and non-medical costs, collected through questionnaires. Main health outcome will be Quality Adjusted Life-Years (QALYs), but other health outcomes including MSIS-29 will also be considered. The return of investment will be assessed using the incremental cost-effectiveness ratio and incremental net monetary benefit.

A per protocol-analysis will be done to evaluate the sensitivity of the main results. Use of at least ≥80% of study drug will be regarded as being compliant to study drug. Study drug adherence will be reported as mean with SD or median with interquartile range.

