### Study design

2.1

A multicenter two arm, 1:1 randomized, triple-blind, placebo-controlled clinical trial comparing metformin versus placebo in patients with non-active PMS will be conducted at 5 sites in Belgium. Participants with PMS, along with caregivers and investigators, will be blinded. We hypothesize that metformin, as add-on treatment in patients with PMS, is able to delay disease progression in comparison to placebo.

Patient recruitment has started in December 2023. After meeting the inclusion criteria and providing written informed consent, a total of 120 patients will be included and randomized 1:1 to either the metformin or placebo group. The randomization will be stratified. The sample size calculation was based on the primary outcome measure, the change in walking speed as measured by the Timed 25-Foot Walk Test (T25FW). The sample size was calculated based on previously reported mean T25FW measurements in PMS patients of 11.2 and 11.5 seconds (22, 58) and the assumption that a 20% change in T25FW is seen as clinically relevant, which amounts to a decrease of on average 2 seconds over 96 weeks (59–62). Using the annualized rate of change described by Spain et al. (58), we estimated a standard deviation (SD) on the change in T25FW from baseline to 96 weeks of treatment of 3.4 s. Assuming a SD of 3.4 s and a significance level of 0.05, an achieved sample size of 47 per group is required to detect a reduction of 2 s in the change from baseline to 96 weeks comparing metformin to placebo with 80% power using a two-sample t-test (63). A sample size of 59 per arm will allow for a 20% drop-out rate.

Patients will complete 6 onsite study visits and 4 remote telephone visits over the course of a 100-week time period (96 weeks of treatment plus 4 weeks for screening), starting with a screening visit (**Figure 1**). Caregivers will also be given the opportunity to engage in the study, by providing information on caregiver strain at the same timepoints as the patient’s onsite visits. Inclusion of caregivers is only possible after a separate signed informed consent. The anticipated conclusion of the study is set for the end of 2026. A more detailed study schedule which also includes substudies can be found in **Supplementary Table 3**

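### The primary t-test on week-96 change uses, absent imputation, only patients measured at week 96; the already planned all-visit mixed model would be the better primary analysis for an intention-to-treat comparison

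*Protocol article*

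**What the plan says.** The Primary outcome measure section reads: "The primary outcome is the change in T25FW from baseline to 96 weeks of treatment". The Analysis section states "Analysis will be conducted based on the intention-to-treat population". If the data are normally distributed, it then fixes the primary test as "an independent samples t-test to compare the alteration in T25FW from baseline to the end of the 96-week treatment period". The one reason given for that test stands in the same sentence: "the primary analysis will entail in first instance (to align with sample size calculation".

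Two models follow as a secondary sensitivity analysis: a regression of the week-96 value on baseline, "plus a linear mixed model with T25FW at all-time points as outcome". The article says that these models give a tighter estimate of the treatment effect. A per-protocol analysis is listed separately.

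The Study design section requires an achieved 47 per group for 80% power to detect a 2 s difference in change (SD 3.4 s, significance level 0.05, two-sample t-test). It adds: "A sample size of 59 per arm will allow for a 20% drop-out rate". Planned enrolment is 120, with six onsite visits.

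**The concern.** Change to week 96 cannot be computed for a patient without a week-96 walk. Unless values are imputed, the primary test therefore sets aside every randomized patient lost before that visit, together with whatever T25FW values they had already given. The planned mixed model can use those values, but it has only a supporting role. The stated reason for preferring the t-test concerns the sample-size formula and not bias or the question the trial asks. A trial can be sized on a t-test and analysed with a model.

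Two things are at stake. One is precision, because observed data go unused. The other is validity. Treatment lasts 96 weeks, the patients enrolled are already progressing, and the outcome is walking speed. The Study medication and dose section says "Common adverse effects include diarrhea, nausea and abdominal pain". Reasons for leaving could therefore differ by arm and be related to the outcome, and a comparison of those who remain would then be biased.

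**Working it through.** **Inputs.** From Study design: difference 2 s, SD of change 3.4 s, significance level 0.05, 47 achieved per group, 20% drop-out, 59 per arm. Sidedness is not stated. Two-sided is assumed because it reproduces 47; one-sided 0.05 would need about 37.

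**1. The plan's own figures.** Standardized effect = 2/3.4 = 0.588. The exact two-sample t calculation gives 46.35 per group for 80% power, so 47, with 80.6% power at 47. Inflation: 47/(1 − 0.20) = 58.75, so 59. Both figures reproduce.

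**2. Who enters the primary test, absent imputation.** 59 × 0.80 = 47.2 per arm, so about 12 per arm do not contribute.

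**3. Precision.** The standard error of the difference is 3.4 × √(2/n). At n = 47 it is 0.70 s; at n = 59 it is 0.63 s. The gap, about 11%, is the most that full recovery of the missing values could give in a change-score comparison. A mixed model using earlier visits would recover part of it. How much depends on the correlation between visits and on which visits include T25FW, and the article text gives neither.

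**4. Possible bias (assumed patterns).** If a fraction p of an arm is missing and would have worsened by d seconds more than that arm's completers, the completers' mean change is too favourable by p × d.

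- *Loss of 25% in one arm and 15% in the other, both informative, d = 1 to 3.4 s.* Net shift (0.25 − 0.15) × d = 0.10 to 0.34 s. With no true effect and 47 per arm, the chance of a significant result is about 5.2% to 7.7% instead of 5%.
- *Loss of 20% in each arm, informative in one arm only, d = 1 to 3.4 s.* Shift 0.20 × d = 0.20 to 0.68 s. The same chance is about 5.9% to 16%.
- *The second pattern with the placebo arm affected and a true 2 s benefit, d = 1, 2 or 3 s.* The apparent difference is 2 − 0.20 × d = 1.8, 1.6 or 1.4 s, and power at 47 per arm is 71.9%, 61.7% or 50.6%.

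The shift favours metformin when informative loss is heavier there, and hides a benefit when it is heavier on placebo.

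**5. Power if all 59 per arm are analysed.** Suppose 20% stop study drug but are still measured, metformin patients who stop keep a fraction r of the 2 s effect, and the SD stays at 3.4 s. The expected difference is 2 × (0.80 + 0.20r).

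| r | Difference (s) | Power at 59 per arm |
|---|---|---|
| 0 | 1.6 | 71.7% |
| 0.25 | 1.7 | 76.8% |
| 0.5 | 1.8 | 81.4% |
| 0.75 | 1.9 | 85.3% |
| 1 | 2.0 | 88.7% |

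The article does not give r.

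**The case against.** The strongest reply is that the article names an analysis set and a test, and nowhere says that patients without a week-96 value are excluded. An imputation rule may stand in the full protocol or the statistical analysis plan, neither of which is shown, and its absence from an article is not a fault. That stands, and it is why the point is conditional on there being no imputation. It does not answer the choice the article does make, which is to rank the all-visit model below the t-test for a reason unrelated to missing data.

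A reader might infer that the drop-out allowance contradicts intention-to-treat. It does not. Recruiting extra patients to cover lost data is ordinary planning and not a rule to delete anyone, and the separate per-protocol analysis shows that selection by adherence is kept apart.

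A reader might also infer that the 80% is wrong, or that about 72% is the true figure. The article ties 80% to 47 achieved per group and does not present it as the power with everyone analysed. The 72% is only the r = 0 end of the range; power is above 80% once those who stop keep about half the effect.

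Finally, arm-specific informative loss is assumed. The article gives no drop-out by arm. It says that the gastrointestinal effects can be largely mitigated and that the dose may be lowered, so intolerance need not mean leaving. Nothing in it says that stopping study drug ends follow-up. The mixed model is not a complete cure either: worsening after the last recorded visit is not recovered under missing at random.

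**Conclusion.** The point holds as a weak choice of primary analysis, not as an error in the stated figures. Absent imputation, the primary test rests on about 47 of 59 patients per arm at the planned loss and ignores earlier values of the rest, while a planned analysis that would use them is secondary. The loss of precision is at most about 11% in the standard error. The bias is a risk and has not been demonstrated: 0.10 to 0.68 s under the assumed patterns, in either direction. The sample size needs no restatement. The documents do not support a claim that the plan contradicts its intention-to-treat label or that its power is misstated.

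**What to change.** - **Primary analysis:** the week-96 treatment contrast from the planned linear mixed model, with baseline T25FW, the randomization strata, visit and treatment-by-visit, in all randomized patients with T25FW data. If baseline enters only as a covariate, patients with no later value add nothing to the contrast; say how they are handled.
- **Sensitivity analysis 1:** the t-test, described as an analysis of patients observed at week 96.
- **Sensitivity analysis 2:** one departure from missing at random, such as a delta or tipping-point analysis.
- **If the t-test stays primary:** state how randomized patients without a week-96 value enter it.
- **Power:** leave the sample-size statement as it is. If power with all 59 per arm analysed is reported, give the range of about 72% to 89% with the assumed effect kept by the 20% who stop.

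The change should be fixed before unblinding. It swaps the roles of two planned analyses and adds one run, with no new patients. The downsides are that the primary test no longer matches the sample-size formula exactly and that the model relies on missing at random, which the second sensitivity analysis is there to probe.

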▪ A diagnosis of non-active progressive multiple sclerosis (including PPMS and SPMS, in accordance with 2017 revisions of McDonald criteria (5) and disease course definitions of Lublin 2013 (68)), as evidenced by: a. the absence of relapses and new T2 lesions and/or enhancing T1 lesions on brain MRI in the past 1- 2 years or longer (NEDA-2) b. progression of disability independent of relapses in the past 1-2 years or longer. If progression is defined as one of the following, over the past 1-2 years or less, the patient can be included without additional review: o minimum increase in the EDSS of 1.0, or 0.5 from a baseline level of 2.0–5.0, and 5.5- 6.0, respectively o ≥20% in the T25W o ≥20% 9HPT o reduction of ≥4 points or a 10% worsening in the Symbol Digit Modality Test without concomitant depression or fatigue ▪ If the investigator is in the opinion that the patient is clearly progressing, but not enough data are available to demonstrate this, a narrative need to be provided, which will be judged by at least 2 members of the trial steering committee, from a center that is not submitting the case for review. ▪ Age 18-70 years inclusive ▪ EDSS 2.0-6.5 inclusive ▪ Able to give informed consent (signed, written) and to adhere to study procedures ▪ Dutch/Flemish speaking ▪ Stable use of DMT or no treatment in the past year or longer ▪ Use of adequate contraceptive measures in women of childbearing potential (WOCBP); no contraception is required for male subjects with pregnant or non-pregnant WOCBP partner.	▪ Diagnosis of diabetes mellitus or fasting glucose level of 126mg/dl or more; random glucose level of 200mg/dl or more; HbA1C of 6.5% or more at screening ▪ A medical or neurological problem other than MS that is a cause of progressive or fluctuating gait dysfunction ▪ Unable to complete T25FW ▪ Unable to undergo MRI ▪ Current major disease or disorder other than MS (e.g., active malignancy, significant renal insufficiency eGFR 3 times ULN, chronic active infection etc.) that may interfere with study procedures and/or intake of study drug ▪ Pregnant or breast-feeding or planning pregnancy ▪ Use of an experimental therapy in the past 6 months ▪ Ongoing immune reconstitution therapy schedule (cladribine second course ended at least 12 months before inclusion, alemtuzumab second/last course at least 12 months before inclusion, AHSCT at least 12 months before inclusion) ▪ Expected change in ongoing DMT or start of DMT if untreated ▪ Current use of metformin or known intolerance for metformin ▪ Known sensitivity to active substance or to any or the excipients ▪ All forms of acute metabolic acidosis (such as lactic acidosis, diabetic ketoacidosis, diabetic precoma ▪ Acute conditions where there is a risk of alteration of renal function, such as: dehydration, severe infection, shock occurring between screening and randomization ▪ Chronic use of NSAID

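### The primary t-test applies only if unspecified data look normal, and the protocol article names nothing to replace it if they do not

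*Protocol article*

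**What the plan says.** The Primary outcome measure section sets a plain change score with no transformation: "The primary outcome is the change in T25FW from baseline to 96 weeks of treatment".

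The Analysis section makes the test conditional: "If the data exhibit a normal distribution, the primary analysis will entail in first instance" followed by "an independent samples t-test to compare the alteration in T25FW from baseline to the end of the 96-week treatment period". The stated reason for the t-test is agreement with the sample size calculation. The same paragraph then lists other models: "A secondary sensitivity analysis will include a linear regression model with 96-week T25FW as outcome and baseline T25FW as predictor", together with a linear mixed model over all time points. Both are labelled as sensitivity analyses and neither is offered as a replacement. No transformation or rank-based test is named anywhere in the article.

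Study design sizes the trial on a two-sample t-test with no condition attached: "Assuming a SD of 3.4 s and a significance level of 0.05, an achieved sample size of 47 per group is required". The target there is a between-arm difference of 2 s in mean change, at 80% power. Relevance is introduced as a percentage, "the assumption that a 20% change in T25FW is seen as clinically relevant", and converted there to about 2 s.

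**The concern.** Three things are open in the conditional sentence.

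- **Which data:** baseline times, 96-week times, change scores or model residuals, pooled or by arm.
- **Which criterion:** a formal test, a plot or a judgement.
- **What follows if it fails:** the sentence is silent, and calling the t-test a first step suggests that another analysis may follow.

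The t-test compares mean changes. A rank test compares the ordering of changes between arms. These are different quantities, so the open branch affects what the trial estimates as well as its p-value. The stated 80% power describes only the t-test branch. At stake is pre-specification of the trial's main result: a reader could not rule out that the reported test was the more favourable of two.

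**Working it through.** **1. The plan's own figure.** Inputs from Study design: difference 2 s, SD 3.4 s, alpha 0.05 (taken as two-sided), power 80%.

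Normal approximation: n = 2 × (1.960 + 0.842)² × 3.4² / 2² = 2 × 7.85 × 2.89 = 45.4, so 46 per arm. With the noncentral t distribution, n = 46.35, so 47 per arm (power 80.6%). Allowing for 20% drop-out: 47 / 0.8 = 58.75, so 59 per arm. Both stated figures reproduce, and both belong to an unconditional t-test in seconds.

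**2. How often would the condition fail, and does failure matter?** The article gives mean times (11.2 and 11.5 s) and the SD of change, but no median, range or skewness for T25FW or its change. The shapes below are therefore assumptions. Setting: 47 per arm, SD of change 3.4 s, normal or shifted log-normal changes, and normality judged by Shapiro-Wilk at 5% on pooled within-arm residuals. Power is for a pure 2 s shift. The last column rejects if either the t-test or the Mann-Whitney test gives p < 0.05. There were 4,000 replicates for power and 20,000 for free choice. Where two values are shown for the other columns, they come from the two sets of runs.

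| Skewness of change | Condition fails | t-test type I error | t-test power | Type I error, free choice |
|---|---|---|---|---|
| 0 | 5% | 4.6–4.8% | 81% | 5.8% |
| 0.30 | 17% | 5.0% | not run | 5.9% |
| 0.78 | 68–70% | 4.9–5.2% | 80% | 6.2% |
| 1.75 | 99.7% | 4.6–5.0% | 82% | 6.8% |
| 3.26 | 100% | 4.6–5.3% | 81% | 7.2% |
| 6.18 | 100% | 4.0% | 83% | not run |

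Skewness is not the only trigger. With symmetric heavy tails (t distribution, 5 df) the condition failed in 54.5% of trials, while the t-test kept 4.9% type I error and 82% power.

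A fixed two-stage rule (t-test if Shapiro-Wilk passes, Mann-Whitney otherwise) gave 4.9–5.1% in these runs. The inflation therefore comes from an unfixed choice. The normality check alone does not cause it.

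**3. Does the result depend on how change is modelled?** Setting: 47 per arm, log-normal baseline with mean 11.4 s and SD about 5 s, Shapiro-Wilk at 5% in each arm. The ranges cover separate runs with slightly different settings.

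| Assumed change | Fails in at least one arm | t-test power | Power of ANCOVA on log T25FW |
|---|---|---|---|
| Proportional (log-SD 0.25) | 86–88% | 83–87% | 89–94% |
| Additive (normal, SD 3.4 s, effect 2 s, 2.5 s floor) | 11–12% | 79% | 73% |

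The failure rate and the ranking of the two scales both follow from the assumed model.

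**4. Does the sample size still cover a baseline-adjusted regression?** Let σ₀ and σ₁ be the SDs at baseline and week 96, and ρ their correlation. The variance of change is σ₀² + σ₁² − 2ρσ₀σ₁. The regression residual variance is σ₁²(1 − ρ²). The first minus the second equals (σ₀ − ρσ₁)², which is never negative. Apart from one degree of freedom, 47 per arm remains sufficient. In the proportional simulation, the regression in seconds had 83.0% power against 82.8% for the t-test.

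**The case against.** The strongest reply is that this is a condensed article. A full protocol or SAP, not shown here, may give the criterion and the fallback. That stands as a limit: the gap is established for this article only. But the article states the conditional rule itself, and a fallback named elsewhere would still leave the primary analysis dependent on the data.

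A second reply is that the harm is small. This also largely stands. A fixed two-stage rule holds about 5%, and even free choice adds only about 0.5 to 2.2 percentage points.

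Three stronger readings are tempting, and the document does not support them.

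- **That the outcome will be right-skewed, so the primary analysis will usually be undefined.** With "EDSS 2.0-6.5 inclusive", a long upper tail in raw times is plausible, but no figure is given. The test is on the change, whose shape need not follow that of the raw times.
- **That a t-test in seconds would be invalid or underpowered.** It kept its error rate and roughly its planned power under every shape in the first table. A rank test had more power under a pure shift with marked skewness (93% against 82% at skewness 1.75), but it estimates something else.
- **That the 20% criterion obliges a log-scale primary analysis.** Study design uses 20% as a relevance threshold and converts it to seconds. It does not say that treatment acts proportionally in each patient.

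**Conclusion.** The point holds in a narrow form. The primary test depends on an undefined normality judgement of the trial's own data, with no alternative named in the article, although the sample size assumes an unconditional t-test. The consequence is a test and estimand not fixed in advance. If the choice between t-test and rank test were free, type I error would be about 5.5% to 7% instead of 5%.

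The probability that the condition fails cannot be computed from the article. The range from about 5% to nearly 100% rests on assumed shapes and an assumed Shapiro-Wilk rule. The conclusion that the condition is unnecessary rests on simulated shapes at 47 per arm, and held for all of them. The choice between seconds and log scale is a trade-off that the article's figures do not settle.

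**What to change.** Before unblinding, delete the normality condition and the wording that makes the t-test a first step. Name one unconditional primary analysis in seconds, the scale of the sample size:

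- **Preferred:** the linear regression of 96-week T25FW on treatment and baseline T25FW, already listed as a sensitivity analysis. Fix its covariates in advance, since the Analysis section leaves further ones open.
- **Otherwise:** the two-sample t-test on change, without condition.

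Name the log-scale (percentage) analysis and a rank-based test as sensitivity analyses, so that skewness is examined without altering the primary result.

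Stating a criterion and fallback while keeping the condition would be a lesser repair: it would control the error rate but leave the estimand dependent on the data.

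The cost is wording only. If the regression becomes primary, Study design needs one sentence saying that the t-test sample size is retained because, apart from one degree of freedom, baseline adjustment does not increase the residual variance.

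### The primary test is an unadjusted t-test on change, chosen only to match the sample-size formula; a baseline- and stratum-adjusted primary analysis would be at least as efficient at the same sample size

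*Protocol article*

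**What the plan says.** The Analysis section (section 3) of the protocol article makes the primary analysis conditional on normally distributed data: "the primary analysis will entail in first instance (to align with sample size calculation) an independent samples t-test to compare the alteration in T25FW". The bracketed remark is the only reason given.

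The same paragraph then lists, as a secondary sensitivity analysis, a linear regression of 96-week T25FW on baseline T25FW and a linear mixed model over all time points. Of these it says: "both models can take other confounders into account) to get a more precise estimate of the treatment effect". Similar regression and mixed models are planned for the secondary and clinical tertiary outcomes, so among the clinical outcomes only the primary one rests on the unadjusted comparison.

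Study design (section 2.1) says of allocation: "The randomization will be stratified". The article does not name the factors, and neither the primary test nor the description of the sensitivity models mentions them.

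The size was planned for the t-test: "an achieved sample size of 47 per group is required to detect a reduction of 2 s in the change from baseline to 96 weeks". The SD entered was 3.4 s, alpha was 0.05 and the target power was 80%.

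**The concern.** The plan identifies analyses that it regards as more precise and then lets a less precise one decide the trial. Alignment with the sample-size formula is a weak reason. A size computed from the SD of the change score remains sufficient, and is usually conservative, when the analysis adjusts for baseline.

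The second part concerns the stratification. Balancing the arms on prognostic factors reduces the true variability of the treatment difference. A t-test that ignores the factors still estimates its standard error from the full between-patient variance, so the interval is wider and the test more conservative than the design warrants.

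At stake is power on a single primary endpoint planned at barely above 80%. If the t-test missed significance and the adjusted model did not, the less efficient result would be the official one, and that ranking could not credibly be changed after unblinding.

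**Working it through.** **Inputs from Study design.** Difference 2 s; SD of change 3.4 s ("we estimated a standard deviation (SD) on the change in T25FW from baseline to 96 weeks of treatment of 3.4 s"); alpha 0.05; power 80%; 1:1 allocation; 20% drop-out. The article does not state sidedness. Two-sided is inferred, because it gives 47 and a one-sided test would need only about 36.

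**Reproducing the plan.** The two-sample t-test with effect size 2/3.4 = 0.588 solves at 46.35, rounded up to 47 per group. The noncentrality at 47 is 2 / (3.4 × √(2/47)) = 2.85 on 92 degrees of freedom, which gives 80.6% power. With drop-out, 47/0.8 = 58.75, hence 59 per arm. The plan's figures are correct for its test.

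**Baseline adjustment.** Let ρ be the correlation of baseline with week-96 T25FW. ρ is not in the document and is assumed here.
- Change-score variance: σ0² + σ1² − 2ρσ0σ1.
- ANCOVA residual variance: σ1²(1 − ρ²).
- With equal SDs the ratio is (1 − ρ²) / (2(1 − ρ)) = (1 + ρ)/2, so the working SD is 3.4 × √((1 + ρ)/2).

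| ρ (assumed) | Working SD (s) | Power at 47 per arm | Cross-sectional SD implied, 3.4/√(2(1 − ρ)) (s) |
|---|---|---|---|
| change score, unadjusted | 3.40 | 80.6% | – |
| 0.6 | 3.04 | 88.4% | 3.8 |
| 0.7 | 3.13 | 86.4% | 4.4 |
| 0.8 | 3.23 | 84.5% | 5.4 |
| 0.9 | 3.31 | 82.5% | 7.6 |
| 0.95 | 3.36 | 81.5% | 10.8 |

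The general form is a variance factor of 1 − r², where r is the correlation of change with baseline; at r = 0 nothing is gained. If variance grows over time the gain can vanish. With the week-96 SD 20% larger and ρ = 0.8, the ratio is 1.44 × 0.36 / (1 + 1.44 − 1.92) = 0.518/0.52 = 0.997, and power is 80.7%. The degree of freedom spent on baseline is negligible.

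**Stratification.** The strata's share of the variance of change is also assumed. Simulation: two equal, exactly balanced strata, 46 per arm, 2 s difference, total SD 3.4 s, 40,000 runs.

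| Share explained | t-test type I error | t-test power | Stratum-adjusted power |
|---|---|---|---|
| 0% | 0.049 | 79.9% | 79.9% |
| 5% | 0.044 | 80.1% | 81.5% |
| 10% | 0.037 | 81.1% | 83.8% |

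A repeat with one million runs and an additive stratum term gave type I errors of 0.044 and 0.039, and powers of 80.3% against 81.7% and 80.9% against 83.7%. The gain is thus about 1.4 points at 5% and about 2.7 at 10%, with the adjusted test at 0.05. The comparison must be with the t-test's own power under balanced strata, because the t-test also benefits somewhat from the balance. The stratum and baseline gains should not be added together, since the strata may overlap with baseline walking speed.

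**The case against.** The best defence is that nothing here is an error. An unadjusted t-test is valid in a randomized trial, ignoring balanced strata makes it conservative rather than liberal, and the 80% target is met on the plan's own assumptions. Both more precise models are prespecified and will be reported, so the precision is ranked lower rather than discarded. All of this stands. A reader might infer that the t-test is biased, that its type I error is inflated or that the trial is underpowered; the documents support none of these.

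The size of the benefit is also uncertain. Neither ρ nor the cross-sectional SD is given, and nothing in the article favours the low-ρ end that yields 88.4%. At ρ = 0.9 the gain is about 2 points. Growing variance is plausible in patients selected for progression, and it could remove the gain. The strata would have to predict change in walking time, not only its level. This also stands: the direction is secure, the magnitude is not.

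A reader might further fault the sensitivity models because they leave additional covariates open. The wording on confounders is loose for a randomized comparison. But it concerns sensitivity models only, and the covariate list is ordinary detail for a statistical analysis plan that is not shown, so it is no part of this point.

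What the defence does not supply is a reason to prefer the t-test as the deciding analysis. Matching the planning formula does not require it.

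**Conclusion.** The point holds as one of efficiency. The article fixes an unadjusted t-test on change as primary, conditional on normality, while ranking the baseline-adjusted model lower and making no use of the stratification. With 47 per arm, baseline adjustment would be worth about 2 to 8 power points (82.5–88.4% against 80.6%) if ρ lies between 0.9 and 0.6 and the variances are equal, and close to none if variance grows. Stratum adjustment would be worth about 1.4–2.7 points if balanced strata explain 5–10% of the variance of change, and nothing if they explain none. Those inputs are assumptions. What does not depend on them is that adjustment gains or is essentially neutral, and that it uses data already collected. It should be changed, but the trial is sound without it.

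**What to change.** Name a single primary analysis: an ANCOVA of week-96 T25FW with treatment, baseline T25FW and the factors used to stratify the randomization. Fix the model before unblinding and remove the condition on normality, so that the choice of primary method does not depend on a test of the trial's own data. Keep the t-test on change and the linear mixed model as sensitivity analyses. Do not leave the ANCOVA and the mixed model as alternatives for the primary analysis, because they treat drop-out differently and 20% is expected.

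The 47 evaluable and 59 randomized per arm can stand as a conservative size. The cost is a wording change in the protocol and the statistical analysis plan; no additional patients, visits or data are needed.
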